### Participant Anonymity

Since participants are required to come to the St. Michael’s Hospital Simulation Centre to complete the virtual reality and wearable components of the study, the study will not be anonymous. Participants will only start using the mobile app after they participate in the virtual reality simulation component of the study. The study coordinator will provide an ID and password by email after participants provide written consent, logistical information (preferred time slot), and demographic information to the study coordinator by email.

### Mobile Data Collection

#### Active Data

The surveys will pop up on fixed days of the week for active data collection (ie, Monday, Wednesday, and Friday), as reminders. The participants are then free to complete the surveys (Table 4). These surveys will allow for monitoring of stress-related symptoms using validated scales—Daily surveys using 15 items taken from the UCLA Loneliness Scale [22] (3 items), PSS [23] (4 items), Generalized Anxiety Disorder [24] scale (2 items), Patient Health Questionnaire [25] (2 items), and MIOS [26] (4 items). Each week, on the weekend, the complete versions of the PSS [23] (10 items), Generalized Anxiety Disorder [24] scale (7 items), Patient Health Questionnaire [25] (9 items), MIOS [26] (10 items). Once during the study, the App Experience Survey (6 items) will be administered.

The content of the Moral Injury Outcome Scale is more specific to reflect the virtual reality scenario, unlike in the mobile study, where the survey is more generalized. The cognitive tests appear similar to electronic games wherein participants have to complete a trail or pattern. We will collect the time and number of errors made by the participants.

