### Security and Privacy of the Study Data

During the session hosted at St. Michael’s Hospital Simulation Centre, data (CSV files, text files, audio, and video files from the session) will be securely uploaded to a password-protected drive. Only specific members of the project have access to the data. Responses on paper questionnaires will be input to a spreadsheet and stored on the encrypted drive. During the longitudinal monitoring part of the study, all active and passive data will be stored on the participant’s phone (if storage space is available) until those data are synced back to the back-end server. Data are transferred over a TLS layer; hence, it is encrypted by RSA Asymmetric Encryption Algorithm.

Study data will be stored for 10 years. No personal information will be collected through the mobile component of the study. Demographic data (ie, age, sex, type of job at Unity Health Toronto, diagnosis, and COVID-19 status) will be collected separately from data collected by the app. A study participant ID will link these data for final analysis.

The server and the dashboard will be hosted on the same virtual machine server, and the database will be hosted on a different database server (Multimedia Appendix 1).

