### Subjective Data Collection

We plan to collect subjective data such as qualitative data from surveys and open-ended feedback. As mentioned in the previous sections, the MISS-HP, IPQ, PSS, and MIOS will be answered throughout the experiment. At the end of the virtual reality session, an exit survey composed of open-ended and 3 multiple choice questions for general feedback.

Overall, the MIOS and PSS are evaluated at the beginning and end of the study for a global assessment of distress (Multimedia Appendix 2), whereas the MISS-HP is collected for a local assessment of distress (Multimedia Appendix 3).

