#### Passive Data

Passive data (GPS and accelerometer data) are collected automatically while the phone is on, even when the participant is not using the phone (Table 4). The app will access information collected and stored on the phone. Participants can opt out of this feature if they choose.

GPS collects data of the participant’s location data with 3-meter accuracy; however, the participant’s specific location will not be used as data in the study. The app collects GPS data constantly, and data are immediately converted into broad summary metrics, such as the distance per day and or unique locations visited. These data are not monitored in real time, and will not be reviewed by and party.

The accelerometer records triaxial acceleration, which can be used to indicate if the participant is running or walking. These data are not monitored in real time.

Participants may receive an automated alert based on established survey cut-offs at the beginning of the study. After some time, these alerts may be based on the participant’s change in scores compared to their own baseline. The alerts will be simple, for example, “your score today suggests mild anxiety, we suggest exercise, mindfulness practice, etc.” If more than 1 alert is required because more than 1 scale has reached the cut-off, the alert will be given once for all the scales.

For active data, we will use visual analog scales (Figure 10). The scale is linear and continuous for the participant to slide on. The scale is subdivided into varying Likert items according to the questionnaire (eg, a scale with 4 items).

We will use predetermined cut-offs (Table 4) to establish the score for each assessment.

Passive data (eg, GPS, accelerometer) will be collected for the first 2 weeks at the beginning of the study to establish a baseline. Members of the research team will be monitoring the in-person data collection for safety concerns. In addition, participants who are inactive will be contacted to remind them of data collection and patients who are having problems will be contact to give technical support.

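### The protocol describes the MIOS as both a global and a VR-specific scale, so a week-8 comparison with the pre-intervention state would, as written, cross two forms

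*Protocol article*

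**What the plan says.** Two sections of the protocol article describe the MIOS.

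- **Subjective Data Collection** places the scale in the VR session: "the MISS-HP, IPQ, PSS, and MIOS will be answered throughout the experiment". It then assigns roles. On the MIOS it says "the MIOS and PSS are evaluated at the beginning and end of the study for a global assessment of distress". The other moral-injury scale is set against it: "whereas the MISS-HP is collected for a local assessment of distress". Here the MIOS is general and the MISS-HP is tied to the situation.
- **Active Data** (Mobile Data Collection) says: "The content of the Moral Injury Outcome Scale is more specific to reflect the virtual reality scenario, unlike in the mobile study". The app survey is described as the more general of the two. Here the MIOS carries scenario-specific content in the VR part and different content in the app.

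Other sections fix the timing. Participant Anonymity states that the app is used only after the VR component. Trial Design has pre-survey data collected at the in-person prebrief. Active Data lists a 4-item MIOS in the daily survey and the complete 10-item MIOS each weekend. The Abstract (Methods) sets app monitoring at 8 weeks and announces a comparison of the short- and longer-term effects of the VR intervention. Compound Intervention says the surveys, the MIOS among them, are there to evaluate how well the educational intervention works.

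**The concern.** A scale whose content is written around one simulated ICU scenario is not a global measure of distress. The two descriptions therefore cannot both be right for the same administration of the MIOS.

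This matters because moral injury is the construct the study is about. If the only pre-intervention MIOS value is on a scenario-specific form and the follow-up values are on a generalised form, a difference between them is partly a difference between questionnaires. Every participant would move from one form to the other in the same order, and there is no comparison group, so nothing in the data could separate the two parts. A baseline on the right form cannot be collected once a participant has been through the session.

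**Working it through.** The article gives no figure to reproduce: no MIOS mean, SD, expected change or linking study. The check is a comparison of the passages.

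**Which moral-injury scales are available, and when**

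1. Before the intervention: the app is not yet in use, so there are 0 app-form MIOS values. Any MIOS value at this point comes from the session.
2. During the 8 app weeks: the listed scales are the UCLA Loneliness items, PSS, Generalized Anxiety Disorder scale, Patient Health Questionnaire and MIOS. Only the MIOS measures moral injury. One full form per weekend gives 8 × 1 = 8 scheduled 10-item scores per participant. With 10 to 15 participants that is 80 to 120 scheduled scores, none with a pre-intervention value on the app form.
3. The MISS-HP is not listed for the app, so it offers no alternative route from baseline to week 8.

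**What a cross-form difference would contain**

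Write the session score as T0 + f(VR) and the week-8 app score as T8 + f(app), where T is the underlying level and f is what the form itself adds. Then

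observed change = (T8 − T0) + (f(app) − f(VR)).

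The second bracket is not identified: there is one group, one order of forms, and no occasion on which both forms are stated to be given together. A larger sample would not remove it. Differences among the weekly app scores do not contain it, because f(app) cancels.

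**What each reading of the conflict implies**

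- *Active Data is right as written.* The session MIOS is VR-specific, and a comparison from pre-intervention to week 8 crosses forms.
- *Subjective Data Collection is right and the MIOS is one global form.* A like-for-like comparison may exist, but the Active Data sentence is then wrong. It also depends on what the end of the study means. If it means the end of the session, it still has to be shown that the session form is the app form.
- *The Active Data sentence was meant for the adapted MISS-HP.* It then names the wrong scale.

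At least one sentence has to change on every reading.

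**The case against.** The strongest objection is that no analysis of MIOS change from session to week 8 is named. The Abstract promises only a general comparison by machine learning and biostatistics, the analysis sections describe feature extraction, classification and association, and efficacy is left to later studies. This stands. A reader might infer that the plan contains an invalid change score; the documents do not support that. What remains is conditional: if longer-term impact on moral injury is judged against the pre-intervention state, the listed instruments give no other route.

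It can also be said that the global MIOS may be a single form used twice (Multimedia Appendix 2 is not shown), or that the VR-specific remark belongs to the MISS-HP, which is called adapted and given the local role. Either is possible and the text cannot settle it, but both require a correction to Active Data.

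Three stronger readings should be set aside.

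- *Paper versus slider.* The article says "Responses on paper questionnaires will be input to a spreadsheet", without saying which questionnaires are on paper. For the app it says "For active data, we will use visual analog scales" and "The scale is linear and continuous for the participant to slide on", but the next sentence divides the slider into each questionnaire's Likert steps. Nothing says that unrounded values are summed, and Table 4 has no MIOS cut-off.
- *A VR-specific form cannot be answered before the scenario.* This depends on item wording that is not shown. Working providers may be able to answer items on ICU scarcity beforehand.
- *A false-positive rate for the form change.* Any such figure would rest on an assumed shift and on a significance test that the article does not plan.

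**Conclusion.** The point holds in a limited form. Subjective Data Collection and Active Data contradict each other on whether the session MIOS is global or scenario-specific. Taking Active Data as written, a comparison of week-8 moral injury with the pre-intervention state would mix a change of questionnaire with real change.

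The size of that mixing cannot be stated from the article. The affected comparison is the one between baseline and app follow-up. Trends within the weekly 10-item scores, and any comparison made on one and the same session form, are not affected.

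The conclusion assumes that the pre-survey MIOS is the session form described under Active Data, and that the longer-term impact on moral injury is meant to be judged against the state before the intervention. In a feasibility study of 10 to 15 people this is a change that should be made, not a fatal flaw. It is worth making because it is cheap and a missed baseline is permanent.

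**What to change.** 1. Reconcile Subjective Data Collection with Active Data: state which MIOS form is given at each time point, and correct whichever sentence is wrong, including the scale name if the MISS-HP was meant.
2. Define the end of the study as the end of the session or week 8.
3. Give the generalised 10-item MIOS, with the same wording and response categories as the app, at the pre-survey and at week 8.
4. If a VR-tailored MIOS is kept, score it separately and do not difference it against the app form.

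The cost is ten extra items at the prebrief, or one questionnaire swapped for another. The article describes the study as ongoing. For anyone whose session took place without the app form, report the weekly app scores as a trend from the first weekend and do not compute a change from the session form.

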#### Passive Data

Passive data (GPS and accelerometer data) are collected automatically while the phone is on, even when the participant is not using the phone (Table 4). The app will access information collected and stored on the phone. Participants can opt out of this feature if they choose.

GPS collects data of the participant’s location data with 3-meter accuracy; however, the participant’s specific location will not be used as data in the study. The app collects GPS data constantly, and data are immediately converted into broad summary metrics, such as the distance per day and or unique locations visited. These data are not monitored in real time, and will not be reviewed by and party.

The accelerometer records triaxial acceleration, which can be used to indicate if the participant is running or walking. These data are not monitored in real time.

Participants may receive an automated alert based on established survey cut-offs at the beginning of the study. After some time, these alerts may be based on the participant’s change in scores compared to their own baseline. The alerts will be simple, for example, “your score today suggests mild anxiety, we suggest exercise, mindfulness practice, etc.” If more than 1 alert is required because more than 1 scale has reached the cut-off, the alert will be given once for all the scales.

For active data, we will use visual analog scales (Figure 10). The scale is linear and continuous for the participant to slide on. The scale is subdivided into varying Likert items according to the questionnaire (eg, a scale with 4 items).

We will use predetermined cut-offs (Table 4) to establish the score for each assessment.

Passive data (eg, GPS, accelerometer) will be collected for the first 2 weeks at the beginning of the study to establish a baseline. Members of the research team will be monitoring the in-person data collection for safety concerns. In addition, participants who are inactive will be contacted to remind them of data collection and patients who are having problems will be contact to give technical support.

**Figure 10 figure10:**

Visual analog scale with a sliding bar for participants to score on the screen of their phones.

**Table 4 table4:** Cut-off values and example notifications.

Assessment and classification				Cut-off values		Example of notification
**Surveys**						
	**General Anxiety Disorder -7**					
		Mild anxiety	5≤score<10		“Based on your scores during the past week, you do not appear clinically anxious/depressed, which is mild/moderate; recommendations include Bibliotherapy, mindfulness, exercise, sleep management”	
		Moderate anxiety	10≤score<15		“Based on your scores during the past week, you do not appear clinically anxious/depressed, which is mild/moderate; recommendations include Bibliotherapy, mindfulness, exercise, sleep management”	
		Severe anxiety	score≥15		“Based on your scores during the past week, you appear clinically anxious/depressed, which is severe; In addition to continued Bibliotherapy, mindfulness, exercise, sleep management”	
	**Perceived Stress Scale**					
		Low	0≤score<14		“Based on your scores during the past week, you do not appear to have increased stress which is mild/moderate; recommendations include Bibliotherapy, mindfulness, exercise, sleep management”	
		Moderate	14≤score<27		“Based on your scores during the past week, you do not appear to have increased stress which is mild/moderate; recommendations include Bibliotherapy, mindfulness, exercise, sleep management”	
		High	score≥27		“Based on your scores during the past 2 week, you appear clinically stressed which is severe; In addition to continued Bibliotherapy, mindfulness, exercise, sleep management”	

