### Mobile Platform

#### Customized Digital intervention/intelligence Group Platform

We will use the app, which is based on an open-source mobile-based platform, LAMP (Learn, Assess, Manage, Prevent [20,21]), which is fully compliant with patient and participant confidentiality standards and is currently in use at various US, Canadian, and international hospitals [20]. Applicable privacy legislation include the Personal Health Information Protection Act of Ontario and The Personal Information Protection and Electronic Documents Act.

Learn: This module offers health tips and accurate health news from sources the participant can trust [20].

Assess: This module infers the participant’s mood and cognitive status (eg, depression, anxiety, etc) by asking the participant to complete surveys. In addition, this module collects the participant’s phone data (eg, geolocation, phone usage).

Manage: In this module, participants can maintain a journal by writing in a diary or have personalized interventions. However, only the participant can write or read the material in this module since all data collected here is personal and available only to the participant.

Prevent: This module uses a dashboard to post figures and curves summarizing the participant’s mood, cognitive status, and phone data, such as how fast the participant is moving.

The app is compatible with both iOS and Android platforms. It will be available for free download and for use by approved participants (log-in information will be provided after obtaining informed consent), and deidentified data will be stored at Unity Health Toronto. Furthermore, the platform will be tailored to collect information pertinent to the COVID-19 context. The platform collects various forms of active data (while the participant is using the app) and passive data (whether or not the user is actively using the app) [20]. Study participants will have the option of full access to their active and passive data in real time on the phone or web-based dashboard.

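### Table 4's example alerts deny increased stress in the PSS Moderate band and break off, in all four severe-range survey rows, before naming the further step

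*Protocol article*

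**What the plan says.** The section on passive data sets the alert rule: "Participants may receive an automated alert based on established survey cut-offs at the beginning of the study". It adds that alerts may later depend on change from the participant's own baseline, and that one alert serves all scales when several reach their cut-offs. Its illustration of an alert reads "your score today suggests mild anxiety, we suggest exercise, mindfulness practice, etc".

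Table 4 then lists cut-offs with an example notification for each band:

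- **PSS Low (0 to below 14) and PSS Moderate (14 to below 27)** carry the same text: "you do not appear to have increased stress which is mild/moderate; recommendations include Bibliotherapy, mindfulness, exercise, sleep management".
- **PSS High (27 and above):** "you appear clinically stressed which is severe; In addition to continued Bibliotherapy, mindfulness, exercise, sleep management", where the message closes.
- **GAD-7 and PHQ-9, mild and moderate bands** share one text: "you do not appear clinically anxious/depressed, which is mild/moderate; recommendations include Bibliotherapy, mindfulness, exercise, sleep management".
- **GAD-7 severe, PHQ-9 moderately severe and PHQ-9 severe** share another: "you appear clinically anxious/depressed, which is severe; In addition to continued Bibliotherapy, mindfulness, exercise, sleep management", where the message closes.
- **Passive data, more than 2 SD from baseline:** the example gives recommendations and then a link to further help.

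On oversight, the same section says "Members of the research team will be monitoring the in-person data collection for safety concerns". The mobile platform section says that participants "will have the option of full access to their active and passive data in real time".

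**The concern.** A message tied to a cut-off should tell the participant which band the score falls in. The PSS Moderate text does the reverse: it tells someone classed as moderately stressed that stress does not appear raised. If the app follows the examples, a PSS of 26 is reported as no increase and a PSS of 27 as severe, with nothing in between.

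The severe-range texts fail differently. Each opens a sentence that promises a step beyond self-help and stops before giving it. These are the scores at which a pointer to help matters most.

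What is at stake is participant information and safety in a group recruited because it may be distressed. During the mobile phase the full PSS, GAD and PHQ scales are completed weekly and remotely. The safety monitoring that the article describes covers in-person data collection, and the offer of a psychotherapist appears under the in-person debrief.

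**Working it through.** No formula or stated figure is involved. The check sets each survey band in Table 4 beside its example text.

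| Scale and band | Scores | What the example text does |
|---|---|---|
| PSS Low | 0 to <14 | Denies increased stress; broadly fits the label, though awkwardly worded |
| PSS Moderate | 14 to <27 | Same text as Low; contradicts the label |
| PSS High | ≥27 | Says severe, then breaks off |
| GAD-7 mild | 5 to <10 | Joint text, ambiguous |
| GAD-7 moderate | 10 to <15 | Joint text, ambiguous; poor fit with the label |
| GAD-7 severe | ≥15 | Says severe, then breaks off |
| PHQ-9 mild | 5 to <10 | Joint text, ambiguous |
| PHQ-9 moderate | 10 to <15 | Joint text, ambiguous; poor fit with the label |
| PHQ-9 moderately severe | 15 to <20 | Says severe, then breaks off |
| PHQ-9 severe | ≥20 | Says severe, then breaks off |

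**Count of bands.** 3 (PSS) + 3 (GAD-7) + 4 (PHQ-9) = 10. By type: 1 fits, 1 contradicts its label, 4 are unfinished and 4 are ambiguous; 1 + 1 + 4 + 4 = 10. The firm defects are 1 + 4 = 5. The Trails B cognitive test is not counted.

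**Reach of the PSS text.** Taking scores as whole numbers, Low covers 0 to 13 (14 values) and Moderate covers 14 to 26 (13 values). One denial therefore serves 14 + 13 = 27 values, 13 of which the table itself classes as moderate.

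**Is the break-off an extraction fault?** Probably not. The same ending, followed by a closing quotation mark, occurs in all four severe-range rows across three scales. The longer passive-data messages are intact, and nothing marks a redaction.

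**Comparison within the article.** The alert illustrated in the passive data section names both condition and band. The joint GAD-7/PHQ-9 text names neither definitely. The large-change passive-data alert shows that a help link was envisaged, but as printed it is attached to a change in phone data and not to a severe depression or anxiety score.

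**The case against.** The strongest reply is that Table 4 is presented as examples in a condensed journal article. The final message strings would normally sit in the app specification or full protocol. This limits the conclusion: a reader might infer that severe scorers are in fact left without a pointer to help, and the article does not show that. It shows an unfinished example. The reply does not remove the point, because the authors chose to print these texts, and one is wrong and four are incomplete as printed.

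Second, the joint GAD-7/PHQ-9 wording can be read as placing the score below clinical level, that is, mild or moderate. The rule of one alert for several scales also suggests a shared template. A reader might call all four rows flatly self-contradictory; the text does not support that, and ambiguity is the fair description. Two difficulties remain. The wording sits badly in rows labelled moderate, and Table 4 assigns it to each scale separately, whereas the one-alert rule applies when several scales reach their cut-offs.

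Third, cut-off alerts are described for the beginning of the study and may later give way to own-baseline alerts. The jump between 26 and 27 on the PSS therefore need not persist through the 8 weeks. That stands.

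Fourth, the alert is not the participant's only information, since access to one's own data is offered. That also stands, but the access is optional and does not complete a broken message.

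Finally, this is a feasibility pilot of 10 to 15 people, and no number of affected participants can be derived. That bears on scale, not on whether the texts should be corrected.

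**Conclusion.** The point holds for the printed examples. The PSS Moderate alert contradicts its own label, and all four severe-range survey alerts stop before the step they announce: 5 of 10 survey-band texts. The GAD-7/PHQ-9 mild and moderate wording is a secondary matter of clarity in 4 further rows.

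The conclusion rests on two assumptions: that the printed table reproduces the authors' text, which the repeated closing marks support, and that the deployed alerts resemble the examples, which the article neither confirms nor denies. It applies only while alerts are based on cut-offs.

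No estimate, sample size, error rate or analysis is affected. It should still be fixed, because the messages go to participants, the safety monitoring described is of the in-person part, and the correction is specific and cheap.

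**What to change.** 1. Reword the PSS Moderate alert so that it states moderate stress.
2. Complete the four severe-range alerts (GAD-7 from 15, PSS from 27, PHQ-9 15 to below 20, PHQ-9 from 20) with a help link or contact. The link in the large-change passive-data alert is a candidate, but the article does not say where it leads, so the sponsor should first confirm that it suits severe scores. If it does not, another contact has to be named.
3. Have the GAD-7 and PHQ-9 alerts, in both the mild and the moderate rows, name the condition and the band, as the passive data section's illustration does.
4. If the deployed app already uses corrected texts, print those in Table 4.

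The cost is an app text edit and an ethics notification, plus the sponsor's check of the link. Sample size and analysis do not change.
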